### 6.2.6.3 Dependent variable

For both definitions of the clearance of cervical HPV infection presented in Section 4.3.1, the clearance of an incident cervical HPV infection will be analyzed by means of a binary variable with the following categories:

- 0 = No clearance of the cervical HPV infection
- 1 = Clearance of the cervical HPV infection

(See Section 4.3.1 and flowchart in Section 8.2 for case definitions and determination of incident cervical HPV infections and their clearance; See Section 8.3.3 for the flowchart of data associated with this objective).

#### **6.2.6.4 Statistical methods**

The clearance of cervical HPV infections (two definitions) will be analyzed using marginal binary-response models such as generalized estimating equation (GEE) regression models for clustered binary responses [Zeger et al., 1988].

These multivariable analyses will allow taking into account that women may contribute to several observations related to different HPV types, resulting in multiple event times, in addition to estimating the simultaneous effects of determinants. The GEE approach will adjust for the dependency caused by the repeated observations on the same subject by estimating robust standard errors for parameter estimates. The appropriate correlation matrix structure accounting for within-subject correlation will be determined at the time of the statistical analysis based on the patterns observed.

Interactions between determinants of interest and the type of cervical HPV infection will be explored by introducing interaction terms between these determinants and a variable categorizing the type of cervical HPV infections as transient or other, 6-month persistent and 12-month persistent (See Sections 4.4.2 and 4.4.3 for the definition of behavioral and clinical determinants and Section 8.5.2 for the list of determinants that will be taken into account in the analysis). In the presence of strong interactions, the analyses will be stratified according to the type of cervical HPV infection.

Results from the multivariable regression models will include odds ratios (95% CI).

Depending on the results, other models taking into account the time between cervical HPV infections and their clearance (i.e. Cox regression models) may be used also as described in Section 6.4.2.5. In such case, cervical HPV infection detected at the last visit will be excluded of the analysis because they will all be censored at day 0.

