#### 4.3.1 Cervical HPV infections

- **Incident cervical HPV infection:** an incident cervical infection with a given HPV type is defined as the new detection of this HPV type (by PCR) at any time point during the follow-up period (i.e. after enrolment in the control arm of study HPV-008).
- **Transient cervical HPV infection:** a transient cervical infection with a given HPV type is defined as the detection of this HPV type (by PCR) at any single time point during the follow-up period followed by a negative sample for that HPV type at the evaluation performed 6 months after the evaluation when the cervical HPV infection was first detected.
- **6-month persistent cervical HPV infection:** a persistent cervical HPV infection (6-month definition) is defined as the detection of the same HPV type (by PCR) in cervical samples at two consecutive evaluations over approximately a 6-month interval. Thus, the algorithmic definition of a 6-month persistent infection is that there exists a sequence of positive samples with the same HPV type, not interrupted by negative samples, such that the total range is more than 5 months ( $> 150$  days). The start of the persistent cervical HPV infection is defined as the date of the first positive sample in the sequence.
- **12-month persistent cervical HPV infection:** a persistent cervical HPV infection (12-month definition) is defined as the detection of the same HPV type (by PCR) at all available time points over approximately a 12-month interval. Thus, the algorithmic definition of a 12-month persistent cervical infection is that there exists a sequence of positive samples with the same HPV type, not interrupted by negative samples, such that the total range is more than 10 months ( $> 300$  days). The start of the persistent cervical HPV infection is defined as the date of the first positive sample in the sequence.
- **Other cervical HPV infection:** other cervical HPV infections than those described above will be considered in the analysis. These infections are cervical HPV infections with duration less than 150 days and cervical HPV infections detected at the last visit and for which it is not possible to determine if they are transient or persistent.

- **Clearance of cervical HPV infection:** two definitions will be used:

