  - *Definition 1:* the clearance of an cervical HPV infection, whether incident, transient or persistent, with a given HPV type is defined as the occurrence of at least **a negative sample** for HPV DNA (by PCR) of that HPV type at the evaluation performed 6 months after the evaluation when the incident or transient cervical HPV infection was detected or when the last positive sample of the 6-month or 12-month persistent cervical HPV infection was detected.
  - *Definition 2:* the clearance of an cervical HPV infection, whether incident, transient or persistent, with a given HPV type is defined as the occurrence of at least **two negative samples** for HPV DNA (by PCR) of that HPV type at the evaluation performed 6 month after the evaluation when the incident or transient cervical HPV infection was detected or when the last positive sample of the 6-month or 12-month persistent cervical HPV infection was detected.

The flowchart in Section 8.2 provides an example of the determination of cervical HPV infection endpoints for a given HPV type.

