## 9.2 Flowchart of cervical HPV infection endpoint determination

[figure not shown]

The following rules will be applied for the determination of cervical HPV infections in case a HPV type is detected at the last known visit of a patient and was not detected at the previous visits:

| Visit v  | Visit v+1 | Visit v+2             | Rule for the determination of cervical HPV infections and clearance             |
|----------|-----------|-----------------------|---------------------------------------------------------------------------------|
| No HPV-X | No HPV-X  | HPV-X
(last visit) | Other cervical HPV infection at Visit v+2
No clearance of HPV-X at visit v+2 |

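### Under clearance Definition 1, the infection type used for interactions and stratification in SAP 6.2.6.4 is determined by clearance itself

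*SAP*

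**What the plan says.** SAP Section 6.2.6.3 codes clearance as a yes/no outcome per infection, "For both definitions of the clearance of cervical HPV infection presented in Section 4.3.1". Section 6.2.6.4 fits GEE models for clustered binary responses. It then explores interactions between determinants and "a variable categorizing the type of cervical HPV infections as transient or other, 6-month persistent and 12-month persistent", and adds: "In the presence of strong interactions, the analyses will be stratified according to the type of cervical HPV infection".

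The pieces that define this variable and the outcome are elsewhere in the SAP:

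- **Transient** (4.3.1): the type is detected "at any single time point during the follow-up period followed by a negative sample for that HPV type", sampled six months later.
- **Clearance Definition 1** (4.3.1): at least one negative sample "at the evaluation performed 6 months after the evaluation when the incident or transient cervical HPV infection was detected", or after the last positive of a persistent infection. Definition 2 asks for at least two negatives.
- **Persistent** (4.3.1): an unbroken run of positives spanning more than 150 days (6-month) or more than 300 days (12-month).
- **Other**: the table in 9.2 labels a single positive at the last visit "Other cervical HPV infection at Visit v+2" and codes it as not cleared. The missing-data table in 4.5.1 does the same when the only later result is a missing one at the last visit.

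Section 9.3.3 keeps all infections in this analysis. Section 6.2.6.4 drops last-visit infections only if Cox models are used. The covariate list for clearance in 9.5.2 does not include infection type.

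**The concern.** A variable used as an effect modifier or stratifier should be known before the outcome is determined. Infection type here is known only after follow-up, and for the transient level it rests on the same negative sample that counts as Definition 1 clearance. The 4.5.1 table shows this directly: one pattern (positive, missing, negative) receives both labels.

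At stake is the reading of any interaction or stratified odds ratio. A reader would take an odds ratio for smoking, region or HPV type among transient or other infections as an effect on early clearance. It would instead describe which infections happened to be first detected at the end of follow-up. Among 6-month persistent infections there may be few or no uncleared infections with which to fit a model.

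**Working it through.** The SAP gives no figure for this step, so there is none to reproduce. The check lists every possible PCR history and applies the SAP's own rules.

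**Inputs.** PCR at Months 0, 6, 12, 18, 24, 30, 36 and 48 (3.2), so eight visits and 2^8 = 256 complete positive/negative patterns for one type. Type and clearance rules are from 4.3.1, 4.5.1 and 9.2.

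**Assumptions.** Visits fall on nominal dates. The three type levels are exclusive, so 6-month means not also 12-month. The next available sample counts for clearance, including Month 48 after Month 36. Definition 2 needs the next two samples negative.

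**Definition 1, complete visits.** One pattern can contain several infections, so the counts below are infections summed over patterns. They are not expected frequencies.

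- Transient (one positive, then negative): starting at Month 0, 2^6 = 64; starting at any of the six visits from Month 6 to Month 36, 6 × 2^5 = 192. Total 256, all cleared.
- Last-visit other (negative at Month 36, positive at Month 48): 2^6 = 64, none cleared.
- 6-month only (two positives six months apart, then negative): 2^5 + 5 × 2^4 = 32 + 80 = 112, all cleared. A run that does not stop there gains a third positive and passes 300 days. The pair Month 36 and Month 48 already spans 12 months.
- 12-month, cleared: run lengths 3 to 7 give 48 + 20 + 8 + 3 + 1 = 80. Uncleared (positive through Month 48): 32 + 16 + 8 + 4 + 2 + 1 + 1 = 64.

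**Definition 2, complete visits.** Transient: 2^5 + 5 × 2^4 = 112 of 256 cleared. 6-month only: 2^4 + 4 × 2^3 = 48 of 112. 12-month: 20 + 8 + 3 + 1 = 32 of 144.

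| Type | Def. 1, complete | Def. 1, visits may be missing | Def. 2, complete |
|---|---|---|---|
| Transient | 256/0 | 4372/0 | 112/144 |
| Other (last visit) | 0/64 | 0/1644 | 0/64 |
| 6-month only | 112/0 | 1274/185 | 48/64 |
| 12-month | 80/64 | 1462/1451 | 32/112 |

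Entries are cleared/not cleared. The missing-visit column covers all 3^8 = 6561 patterns of positive, negative or missing. Under Definition 1, every uncleared infection in either column is one still positive at the last observed visit.

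**What the first-stratum odds ratio measures.** In a simulation with assumed inputs, two groups had the same clearance probability (30%, 50% or 70% per six months). In one group first detection was shifted to later visits, by a weight of exp(0.1) or exp(0.2) per visit. The Definition 1 odds ratio among transient or other infections was 0.53 to 0.74, although clearance did not differ. A group with truly slower clearance (35% against 50%) and no shift in timing gave 0.74. The stratum cannot tell the two situations apart.

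**The case against.** A reader might infer that clearance is fixed within every stratum. It is not. Under Definition 1 it varies in the 12-month stratum (80/64). In the pooled transient or other stratum it also varies, because that level mixes fixed ones with fixed zeros. Under Definition 2 it varies in all three strata, and only the last-visit infections within the first stay fixed. What predicts clearance once an infection has lasted more than 300 days is a legitimate question, and the persistence definitions do not themselves mention a later negative.

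A reader might also infer that the first-stratum model cannot be estimated. That would need last-visit infections to be removed, and Section 9.3.3 keeps them for the GEE analysis.

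Nor do the documents support saying that the definitions will force the stratified analysis to become the reported clearance result. The step is exploratory and conditional, and type is not a covariate in 9.5.2. In one simulated setting (50% clearance, stronger shift) the odds ratio was 0.55 in the first stratum, 0.57 in the 12-month stratum and 0.55 over all infections. So that distortion comes from coding last-visit infections as uncleared, which is a separate matter, and by itself it does not create a large interaction.

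These limits stand. What remains is that the SAP commits to exploring, and possibly stratifying by, a variable that under Definition 1 is outcome information for two of its three levels. It sets no criterion for a strong interaction.

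**Conclusion.** The concern holds for Definition 1. Type determines clearance completely for transient infections (always cleared) and last-visit infections (never cleared). It does so for 6-month-only persistent infections when visits are complete, and nearly so otherwise: among patterns with missing visits 185 of 1459 are uncleared, all still positive when observation ended. Odds ratios in the first stratum reflect timing of detection and end of follow-up, and the 6-month stratum is close to separation.

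The 12-month stratum and Definition 2 are affected less directly. Clearance varies there, but type is still known only after follow-up, and a transient infection already holds one of the two negatives that Definition 2 requires. The GEE model without this term does not have this defect.

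The result rests on the assumptions listed with the counts. If a Month 48 negative after a Month 36 positive were not accepted as the sample 6 months later, the 2^4 = 16 runs covering Months 30 and 36 would move the 6-month row from 112/0 to 96/16. Repeat positives within 150 days, which 4.3.1 also places under other, do not arise on nominal dates, and the SAP does not say how many there are.

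**What to change.** In Section 6.2.6.4, delete the interaction with, and the stratification by, the three-level infection type. That alone removes the defect and costs only SAP wording.

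If early versus late clearance is of interest, replace the step as follows:

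- Use one record per infection per sampling interval while the infection is still positive at the start of the interval, with the same GEE approach and robust errors.
- Interact determinants with the duration already observed at that point (first interval after detection; 6 to under 12 months; 12 months or more).
- Include a term or offset for interval length, since Month 36 to Month 48 is 12 months and the other scheduled intervals are 6.
- Run it for both definitions: next sample negative; next two samples negative, limited to intervals with two later samples.

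Alternatively, use the time-to-clearance Cox model that 6.2.6.4 already allows, with infection duration as the time scale.

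The cost of the interval model is a restructured dataset from the same data and software, with effects expressed per interval rather than per infection.

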### **6.2.7 Analysis of time to first detected cervical HPV infections**

#### **6.2.7.1 Population**

The population for the analysis of time between the start of sexual activity and a first detected incident cervical HPV infection (or a first confirmed 6-month cervical HPV infection) will be restricted to subjects from the TVC-1-Control arm cohort for whom the date of start of sexual activity is known (i.e. either collected or computed, so that a starting date is available for the computation of the time between the start of sexual activity and a first detected cervical HPV infection) and for whom the date of start of sexual activity is either less than 6 months prior to their inclusion in the study or during the follow-up period.

Subjects with cervical HPV infections preceding the start of sexual activity will not be taken into account in the analyses.

#### **6.2.7.2 Analysis unit**

The statistical unit for this analysis will be the subject.

### 6.2.7.3 Event variable

The analyzed event - first incident cervical HPV infection (or a first confirmed 6-month cervical HPV infection) - will be analyzed by means of a binary variable with the following categories:

- 1 = First detected cervical infection following the start of sexual activity
- 0 = No detection of cervical HPV infection following the start of sexual activity

The event will be determined as showed with the following examples (See section 8.4.3 for more details):

| Sub-
ject* | Detected cervical HPV infections**
over the follow-up period
(in chronological order)                                                                                                                   | Subject
included
in analysis
population | Event
(first
infection)
(0 = No /
1 = Yes) | Event
(first
persistent)
(0 = No /
1 = Yes) |
|---------------|---------------------------------------------------------------------------------------------------------------------------------------------------------------------------------------------------------------|--------------------------------------------------|--------------------------------------------------------|---------------------------------------------------------|
| A             | -                                                                                                                                                                                                             | Yes                                              | 0                                                      | 0                                                       |
| B             | Transient infection associated with HPV type X
Transient infection associated with HPV type Y                                                                                                              | Yes                                              | 1                                                      | 0                                                       |
| C             | Transient infection associated with HPV type X
Transient infection associated with HPV type Y
12-month persistent infection associated with HPV type Y                                                  | Yes                                              | 1                                                      | 1                                                       |
| D             | Transient infection associated with HPV type X
Transient infection associated with HPV type Y
Transient infection associated with HPV type X
6-month persistent infection associated with HPV type X | Yes                                              | 1                                                      | 1                                                       |

\* It is assumed that a date of start of sexual activity is available for all subjects.

\*\* Cervical HPV infections of same HPV type are separated by a clearance.

(See Section 4.3.1 and flowchart in Section 8.2 for the definition and determination of incident, transient, persistent and other cervical HPV infections ; See Section 8.3.4 for the flowchart of data associated with this objective).

### 6.2.7.4 Time computation

The time to a first detected incident cervical HPV infection (or a first confirmed 6-month cervical HPV infection) following the start of sexual activity will be calculated in days as: Date of event or Date of censoring - Date of start of sexual activity.

The date of start of sexual activity will be determined as follows:

- For subjects who already had sexual intercourse prior to study entry: the date of start of sexual activity will correspond to the birthdate collected in the CRF plus the age at first sexual intercourse collected in the baseline behavioral questionnaire,.
- For subjects who did not have sexual intercourse prior to study entry: the date of start of sexual activity will correspond to the maximum between i) the date of the yearly questionnaire in which subjects reported having first sexual intercourse (or the date of the visit corresponding to the yearly questionnaire if the date of the questionnaire is missing) and ii) the date of the preceding detected cervical HPV infection, minus the date of the preceding questionnaire (or visit), divided by 2. In case there is no preceding questionnaire (i.e. baseline questionnaire is missing and first sexual intercourse is reported in the 1-year questionnaire), the date of start of sexual activity will be equal to the date of the 1-year questionnaire (or visit) minus 6 months.

The date of event will be:

- the date of the detection of the first incident cervical HPV infection (or the date of onset or the first confirmed 6-month cervical HPV infection) during the 48-month follow-up period,

The date of censoring will be:

- the date of Month 48 visit for cervical HPV infections of subjects who attended all visits during the 48-month follow-up period and did not have any cervical HPV infection during this period,
- the date of the last PCR reported at the latest visit for which data are available or the date of the last cytology (if the date is after the date of the last PCR) for cervical HPV infections of subjects who did not attend all visits during the 48-month follow-up period and who did not have any cervical HPV infection throughout their follow-up period (from first to last visit).

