### 3.2 Study procedures resulting in data to be used for analyses

- Blood samples for all subjects were drawn at Months 0, 7 and 24 and in a subset of subjects from selected study sites.
- Gynecological examinations were performed at Months 0, 12, 24, 36 and 48.
- Cervical liquid-based cytology samples were collected at Months 0, 6, 12, 18, 24, 30, 36 and 48:
  - HPV DNA typing by PCR was performed on cervical liquid-based cytology samples at Months 0, 6, 12, 18, 24, 30, 36 and 48,
  - Cytopathological examinations were performed on liquid-based cytology samples to detect abnormal cells at Months 0, 12, 24, 36 and 48 in all subjects,
  - Screening for *Chlamydia trachomatis* and *Neisseria gonorrhoeae* on liquid-based cytology samples at Months 0, 12, 24, 36 and 48.

Note: As of Protocol Amendment 2, screening for *Neisseria gonorrhoeae* was done only if considered appropriate by the investigator.

- Colposcopic referral according to appropriate clinical management algorithms. A central laboratory processed and interpreted results from liquid-based cytology and histology samples. All CIN endpoints were confirmed by an expert histopathology review panel that was blinded to vaccine status, HPV DNA status before biopsy and cytology reports. An Endpoint Committee was responsible for reviewing all available clinical and laboratory data prior to study unblinding by the external statistician to make final case assignments for all subjects assumed to meet criteria for primary and secondary efficacy endpoints.

- Behavioral questionnaire completed by interview for all subjects at Months 1, 12, 24, 36 and 48. The behavioral questionnaire (self-administered) collected specific socio-demographic and behavioral data concerning determinants that are recognized to predispose subjects to cervical HPV infection or are recognized co-factors for cervical carcinogenesis. The baseline questionnaire assessed at Month 1 collected data which occurred during past history and during the previous year. Questionnaires assessed at Month 12, 24, 36 and 48 collected data assessed during the previous year.

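### The start-of-sexual-activity rule in SAP 6.2.7.4 yields a duration instead of a date, and taking the maximum disables its infection term

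*SAP*

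**What the plan says.** Time to first infection "will be calculated in days as: Date of event or Date of censoring - Date of start of sexual activity" (SAP 6.2.7.4), so the origin has to be a calendar date. For women who had not had intercourse before entry, "the date of start of sexual activity will correspond to the maximum between i) the date of the yearly questionnaire in which subjects reported" first intercourse, and "ii) the date of the preceding detected cervical HPV infection, minus the date of the preceding questionnaire (or visit), divided by 2". If there is no preceding questionnaire, a separate rule applies: "the date of start of sexual activity will be equal to the date of the 1-year questionnaire (or visit) minus 6 months".

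Eligibility uses the same date. Section 6.2.7.1 requires debut less than 6 months before inclusion or during follow-up, and adds: "Subjects with cervical HPV infections preceding the start of sexual activity will not be taken into account in the analyses".

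The schedules are in section 3.2: "Behavioral questionnaire completed by interview for all subjects at Months 1, 12, 24, 36 and 48", and PCR typing at Months 0, 6, 12, 18, 24, 30, 36 and 48. Annex 9.4.3 gives a worked example (subject #3): debut at Month 6, first infection at Month 24, time 18 months.

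**The concern.** The computed date is both the time origin and an entry criterion for two secondary objectives in section 2.2 (first incident infection, first 6-month persistent infection). As written it cannot be programmed. Whoever programs it must choose a repair, and different repairs give different populations and times.

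The infection term appears to be there for women found HPV-positive before they reported debut. Combined through a maximum, it cannot do that job. Those women then either fail the exclusion rule in 6.2.7.1, which removes them from both analyses, or enter with almost no follow-up time. Whether they are included would then turn on their own outcome and on a few days of visit timing.

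**Working it through.** **Inputs** (SAP 3.2 and 6.2.7.4), in months on the nominal schedule. Qk is the questionnaire reporting first intercourse, Qk-1 the one before it, and D the first HPV-positive sample after Qk-1 and no later than Qk.

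**1. The plan's own figure.** Subject #3: 24 − 6 = 18, as stated. An origin at Month 6 agrees with the fallback (12 − 6 = 6) and nearly with the midpoint of the Month 1 and Month 12 questionnaires: (1 + 12)/2 = 6.5, giving 24 − 6.5 = 17.5. A mid-interval date was evidently intended.

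**2. The rule as written.** (max(Qk, D) − Qk-1)/2 gives (12 − 1)/2 = 5.5 for the first interval and (24 − 12)/2 = 6 for each later one. These are half-lengths of intervals. Nothing is added back to make a date.

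**3. The operator.** D is never later than Qk, so max(Qk, D) = Qk in every scheduled case. The infection date can change the result only through a minimum.

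**4. Possible repairs.** Each cell gives origin; time to detection.

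| Qk-1 to Qk | D | Midpoint with maximum | Halving applied to item ii only | Midpoint with minimum |
|---|---|---|---|---|
| 1 to 12 | 6 | 6.5; −0.5 | 12; −6 | 3.5; 2.5 |
| 1 to 12 | 12 | 6.5; 5.5 | 12; 0 | 6.5; 5.5 |
| 12 to 24 | 18 | 18; 0 | 24; −6 | 15; 3 |
| 12 to 24 | 24 | 18; 6 | 24; 0 | 18; 6 |
| 24 to 36 | 30 | 30; 0 | 36; −6 | 27; 3 |
| 24 to 36 | 36 | 30; 6 | 36; 0 | 30; 6 |
| 36 to 48 | 48 | 42; 6 | 48; 0 | 42; 6 |

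Negative times lead to exclusion under 6.2.7.1. Under the midpoint reading the last interval escapes because no Month 42 PCR is scheduled. (Annex 9.4.3 shows a Month 42 column, but sections 3.1 and 3.2 list no such visit.)

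**5. Rough size.** The SAP gives no debut or infection rates, so a simulation assumed debut uniform over Months 1 to 48, an infection hazard of 0.1 to 0.8 per year, and visit variation from 0 to ±1 month. Under the midpoint-with-maximum reading:

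- About 5 to 9% of first-infection events in women with on-study debut are detected at a mid-interval visit.
- Of those, 25 to 57% are excluded. Most of the rest get under 1 month.
- Their mean true time from debut to detection is about 3.8 months, against about 7.3 months for women detected at the reporting questionnaire. The minimum rule gives the mid-interval group about 2.9 to 3.0 months on average.

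**The case against.** **The intent is clear.** A programmer would read the rule as a midpoint, as the fallback and the worked example suggest. That much stands. But a midpoint does not settle the choice between maximum and minimum, and it is the maximum that produces the exclusions and zero times.

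**The Month 6 exclusion rests on half a month.** It does: 6.5 against 6 on nominal dates. Where the fallback applies, the origin is Month 6 and the time is 0. Hence the finding is exclusion or near-zero time, with visit timing deciding which.

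**The minimum makes the origin depend on the outcome.** A woman positive at Month 18 gets an origin at Month 15, while an uninfected woman with the same questionnaires keeps Month 18. This is a real cost of the fix and calls for the sensitivity analysis below.

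**Two stronger readings that the document does not support.** A reader might infer that the women infected soonest after debut are systematically removed, so that time to infection is overstated. Under the midpoint reading only first infections found at Month 6, 18 or 30, before debut is reported, are affected. A woman who starts late in an interval and is infected quickly is detected at the questionnaire visit and gets 5.5 to 6 months. In the simulation the mid-interval group was only about 26 to 29% of women infected within 3 months of debut. Exclusions and zero times also pull in opposite directions, and no net effect has been calculated.

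A reader might also infer that the rule for debut before entry, "the birthdate collected in the CRF plus the age at first sexual intercourse collected in the baseline behavioral questionnaire", is an error because it places debut on a birthday. The resolution at which age was collected is not shown. If it is completed years, with uniform birthdays and debut dates, the rule keeps about 25% of women whose true debut was within 6 months before entry, but admits none with earlier debut. A mid-window date keeps about 75% but also admits about 25% of those with debut 6 to 12 months before entry. That is a trade-off between sample size and specificity.

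**Conclusion.** The rule is wrong as written and must be corrected before it is programmed. That it yields a duration and that the infection term is inert follow from the text and the visit schedule alone. The consequence depends on the repair: under the midpoint reading, −0.5 months at Month 6 and 0 at Months 18 and 30. If only item ii is halved, mid-interval infections fall at −6 months and those at the reporting questionnaire at 0, in the last interval too.

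The scope is narrow: women with no intercourse before entry, in the two secondary analyses of section 6.2.7. The primary CIN2+ analysis, the other lesion analyses and the clearance analysis do not use this date. The 5 to 9% share rests on simulation assumptions that are not in the SAP.

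**What to change.** Replace the sentence for women without intercourse before entry by: start = preceding questionnaire date + [min(reporting questionnaire date, first HPV-positive date after the preceding questionnaire) − preceding questionnaire date]/2. The restriction to positives after the preceding questionnaire matters; earlier infections remain excluded under 6.2.7.1. State also how a Month 6 positive is handled when the fallback applies, since it sits at time about 0 there.

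Add a sensitivity analysis with the origin at each end of the interval. For the mid-interval women the early end gives 6 − 1 = 5, 18 − 12 = 6 and 30 − 24 = 6 months, and does not use the infection date. The late end gives 0, so the plan should say that these women stay in. Report how many women are excluded for infection before the computed origin.

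The birthday rule need not be replaced. At most, vary the pre-entry debut date within the reported year of age as a further sensitivity analysis.

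The cost is one sentence, one derivation and the sensitivity runs. Section 7 places this analysis in the first quarter of 2012, after the other endpoints. The remaining downside is that the origin is still imputed and, under the minimum, depends on the infection date.
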